### Study design

This is a type 2 hybrid effectiveness-implementation research study examining an integrated RMNCH intervention. This intervention integrates the five evidence-based approaches described above, focused on the “golden 1000 days” from conception through age two. We plan to study the impact on population health outcomes using a pre-post quasi-experimental design with stepped implementation as it is rolled out by CHWs in Achham and Dolakha. We will assess the implementation process using the RE-AIM framework, closely examining reach, efficacy, adoption, implementation, and maintenance.

We will evaluate the intervention as it is rolled out in stepped implementation. Implementation will occur in sub-populations of about 20,000 at a time (including village clusters of 1000 to 6000 people). Full implementation of the integrated intervention in any sub-population will take 6 months. Approximately 80 clusters across the two sites will be involved in the study, with a total population of approximately 300,000. This is incorporated into the power calculations below.

In this pragmatic trial, village cluster units are determined by Nepal administrative boundaries. Enrollment and timing of enrollment are based upon local government decision-making and as such cannot be randomized. Data collection is developed and integrated within the routine course of care, because this is the approach we have found to be ethical, acceptable, and affordable in our context. This has the following implications: (1) the number of villages per cluster is variable, (2) interval between new clusters being ramped up can be variable from the scheduled start times, and (3) baseline data occurs at the beginning of each step rather than at study start.

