### Sample size

This implementation research study uses a census methodology rather than a representative sample. The programmatic intervention aims to reach all individuals within the catchment area population given the research performance site’s care mandate to serve this population. All individuals in the catchment area population, as defined under study site above, who meet the inclusion criteria will be approached for inclusion into the programmatic intervention, for which their de-identified clinical data will be analyzed towards the primary aim. The sample size is determined by the overall population covered in the two districts of 300,000, (rather than calculated via a sample size formula) within which we anticipate approximately 8000 deliveries per year or 12,000 during the first 18 months of the study during which enrollment will occur.

To calculate power for the primary outcome of institutional birth rate, we consider a Poisson regression model with 0.05 significance level and two-sided power of 80 or 90%. We further assume a 1-year exposure mean per child over the course of the intervention. We will consider models where the secular trend and other covariates explain 25 or 50% of the total variance in mortality. We assume intra-cluster correlation of outcomes would range from 0.2 to 0.8 for design considerations. Based on these parameters and recent advances in stepped wedge methodology [47], we calculated a design effect ranging from 0.3 to 0.8 to account for the wedge design. To be conservative, we further included a multiplicative design effect of 2.5 to account for cluster randomization, resulting in an overall design effect of 1.8 at a maximum.

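### The clustering factor of 2.5 does not follow from the assumed ICC of 0.2 to 0.8, so the maximum design effect of 1.8, presented as conservative, is unsupported

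*Protocol article*

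**What the plan says.** The Sample size section of the protocol article sets the correlation first: "We assume intra-cluster correlation of outcomes would range from 0.2 to 0.8 for design considerations". From this and its other parameters, using published stepped-wedge methods, it reports: "we calculated a design effect ranging from 0.3 to 0.8 to account for the wedge design". As a step that it calls conservative, it adds: "we further included a multiplicative design effect of 2.5 to account for cluster randomization", "resulting in an overall design effect of 1.8 at a maximum".

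The size of the study is given in two places. Study design says: "Approximately 80 clusters across the two sites will be involved in the study, with a total population of approximately 300,000". Sample size says: "we anticipate approximately 8000 deliveries per year or 12,000 during the first 18 months of the study". The power criteria are: "we consider a Poisson regression model with 0.05 significance level and two-sided power of 80 or 90" per cent.

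The section gives no cluster size for the factor of 2.5 and no reference design for the wedge factor. It reports no baseline rate, achieved power or detectable change. The number of births is set by a census, not by a formula.

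**The concern.** A clustering factor is determined by the ICC and the number of births per cluster. The article states or implies both, and 2.5 does not come from them. A high ICC shrinks the wedge factor when cluster effects are constant, while 2.5 read as an ordinary clustering factor matches a very low ICC. The combined figure therefore rests on two different pictures of the same clustering.

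At stake is what change in institutional birth the study can detect. A reader told that 1.8 is a conservative maximum would take 12,000 / 1.8 = 6,667 effective births as a floor.

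**Working it through.** **1. The plan's own figure.** 0.3 × 2.5 = 0.75 and 0.8 × 2.5 = 2.0. The maximum is 2.0, not 1.8. Reaching 1.8 needs a wedge factor of 1.8 / 2.5 = 0.72 or a clustering factor of 1.8 / 0.8 = 2.25.

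**2. The clustering factor against the stated ICC.** Births per cluster are m = 12,000 / 80 = 150. The usual parallel-cluster factor is 1 + (m − 1) × ICC.
- ICC 0.2: 1 + 149 × 0.2 = 30.8. ICC 0.8: 1 + 149 × 0.8 = 120.2.
- Solved for 2.5: ICC = 1.5 / 149 = 0.010.
- Smaller units at ICC 0.2: 25 births (a 3-month cell, 8000 / 80 / 4) give 5.8; 40 births (a 1000-person cluster, 1000 × 12,000 / 300,000) give 8.8; 100 births (one year) give 20.8.
- 2.5 needs 1 + 1.5 / 0.2 = 8.5 births per cluster at ICC 0.2, or 1 + 1.5 / 0.8 = 2.9 at ICC 0.8.

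**3. The total design effect, calculated directly.** The model has fixed period effects, a cluster effect, 80 clusters spread evenly over K steps, K + 1 periods, and n = 150 / (K + 1) births per cluster-period. The variance of a cluster-period mean is ICC + (1 − ICC) / n. The covariance between two periods of one cluster is ICC × CAC, where CAC is the cluster autocorrelation. The generalised least squares variance of the intervention effect is divided by 4 / 12,000, the variance for a 1:1 individually randomised comparison.

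With constant cluster effects (CAC = 1) this reduces to

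(K + 1) × [1 + ICC(Kn + n − 1)] / [1 + ICC(Kn/2 + n − 1)] × 3(1 − ICC) / [2(K − 1/K)].

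Example with K = 5, n = 25:
- ICC 0.2: 6 × (30.8 / 18.3) × (2.4 / 9.6) = 2.52
- ICC 0.8: 6 × (120.2 / 70.2) × (0.6 / 9.6) = 0.64
- ICC 0.01: 6 × (2.49 / 1.865) × (2.97 / 9.6) = 2.48

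Over K = 3 to 15 (15 is 300,000 / 20,000 per step; the lower values are assumed):

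| ICC | CAC 1 | CAC 0.95 | CAC 0.8 |
|---|---|---|---|
| 0.2 | 2.37–2.84 | 2.63–4.13 | 3.41–7.87 |
| 0.8 | 0.60–0.72 | 1.73–6.07 | 5.07–21.54 |

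At ICC 0.01, the value that 2.5 implies, the total with constant effects is 2.2 to 2.9. With 24,000 births (8000 × 3 years) the constant-effect results hardly change (2.4–2.9 and 0.6–0.7), but drift costs more, up to 13 at ICC 0.2 and 42 at ICC 0.8.

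**4. What this does to precision.** The detectable difference scales with the square root of the design effect. Relative to 1.8:
- ICC 0.2, constant effects: √(2.37/1.8) = 1.15 to √(2.84/1.8) = 1.26
- ICC 0.2, drift: √(2.63/1.8) = 1.21 to √(7.87/1.8) = 2.09
- ICC 0.8, constant effects, upper end: √(0.72/1.8) = 0.63

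As an illustration, assume a baseline of 50%, 6,000 against 6,000 births and 80% power, so the difference is 2.80 × √(0.5 × DE / 6000). This is 3.4 points at 1.8, 3.9 to 4.3 at 2.37 to 2.84, and 7.2 at 7.87.

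**The case against.** The strongest reply is that the ICC has already been used. The wedge factor is said to be based on the listed parameters, and 2.5 is a further multiplier. If the wedge factor is relative to individual allocation, multiplying by 30.8 would count clustering twice. This stands, and it disposes of a tempting stronger reading: that the true design effect is 0.8 × 30.8 = 24.6, with 12,000 / 24.64 = 487 effective births and a loss of more than tenfold. Those figures hold only if the wedge factor is relative to a parallel cluster design, which the article does not say. The direct calculation at ICC 0.2 does not come near 24.6. Nor does the text show that each factor was picked because it was favourable; adding 2.5 makes the result less favourable than leaving it out.

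It is also true that 1.8 is generous at ICC 0.8 with constant cluster effects.

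A further defence is that covariates are assumed to explain 25 or 50% of the variance (stated for mortality). Applied as a simple multiplier at ICC 0.2 with constant effects, this gives 0.75 × 2.37 = 1.78 to 0.75 × 2.84 = 2.13, or 1.19 to 1.42 at 50%. That could bring some cases under 1.8, but the article does not say that the design effect includes it, and a stated maximum must also cover the 25% case and drift.

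Finally, an article may leave derivations to a fuller document. But these figures are printed, they do not multiply out, and the word conservative is a claim made here.

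**Conclusion.** The point holds in limited form. The factor of 2.5 is not derivable from the stated ICC and births per cluster, the reference design of the wedge factor is not stated, and the stated maximum does not equal the product of its parts. The maximum of 1.8 is therefore unsupported as a conservative figure.

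The direct calculation exceeds it at ICC 0.2, at the ICC that 2.5 implies, and in nearly all drift scenarios; it is met at ICC 0.8 if cluster effects are constant. At ICC 0.2 the detectable difference is about 15 to 26% larger than 1.8 implies with constant effects, and up to about twice as large with drift.

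These sizes rest on my assumptions: the number of steps, even rollout, equal clusters, autocorrelations of 0.95 and 0.8, a linear-model approximation and no credit for covariates. The study's own power cannot be reproduced, because no baseline rate or achieved power is given. The finding does not show that the study is underpowered.

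**What to change.** - State one ICC range for institutional birth, checked against birth data already held (for example the earlier evaluation in a population of 33,000), and the expected births per cluster-period.
- Derive the total design effect from a single stepped-wedge variance formula that allows cluster effects to vary over time. Name the reference design, the number of steps and the assumed autocorrelation.
- Replace 0.3 to 0.8, 2.5 and 1.8 with that result. Do not put 31 to 120 in place of 2.5.
- Drop the word conservative unless the calculation shows it. In the same sentence, reword the reference to cluster randomisation, since Study design says that enrolment timing cannot be randomised.
- Restate the power, or the detectable change in institutional birth, with the baseline rate used.

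The cost is a recalculation and a rewritten paragraph. The stated design effect may become less favourable. The births come from a fixed census, so no extra recruitment follows.

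### The stated maximum design effect of 1.8 does not agree with the two factors it is built from: 0.8 × 2.5 is 2.0 (minor; reconcile the three figures)

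*Protocol article*

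**What the plan says.** The Sample size section of the protocol article first sets out planning assumptions for power on the primary outcome, institutional birth rate. It then builds an overall design effect in two steps.

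- Step one, the stepped-wedge factor: "we calculated a design effect ranging from 0.3 to 0.8 to account for the wedge design".
- Step two, a further inflation: "we further included a multiplicative design effect of 2.5 to account for cluster randomization".
- The result: "resulting in an overall design effect of 1.8 at a maximum".

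The same section says that the number of participants follows from the population covered, "rather than calculated via a sample size formula", and expects "approximately 8000 deliveries per year or 12,000 during the first 18 months of the study". It reports no achieved power, detectable difference or required sample size. The overall design effect is therefore the only derived figure that the power paragraph gives.

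The Study design section says that the timing of enrollment depends on local government decisions and cannot be randomized. The Discussion lists the absence of randomization as a limitation.

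**The concern.** The text says how the two factors combine (by multiplication) and which end of the range is meant (the maximum), so the reader can do the sum. It does not come out at 1.8. The figure is introduced as the conservative case and labelled a maximum, so a reader will take it as the worst case for planning. On the factors as printed it is lower than that worst case, which is the favourable direction. What is at stake is whether any power calculation behind the article used a design effect that is somewhat too small.

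A smaller matter sits in the same sentence. The 2.5 is attributed to cluster randomization, although nothing in this study is randomized.

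**Working it through.** **Inputs, all from the Sample size section.** Wedge factor w = 0.3 to 0.8; clustering factor c = 2.5, described as multiplicative; stated overall maximum = 1.8; alpha 0.05 two-sided; power 80% or 90%; 12,000 deliveries in the first 18 months.

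**1. Attempt to reproduce 1.8.** Overall design effect = w × c.

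- Lower end: 0.3 × 2.5 = 0.75
- Upper end: 0.8 × 2.5 = 2.0

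The stated maximum is not reproduced. Solving backwards, 1.8/2.5 = 0.72 and 1.8/0.8 = 2.25. Neither value is in the text.

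**2. Rounding.** If 0.8 stands for anything from 0.75 to 0.85, the product with 2.5 is 1.875 to 2.125, which excludes 1.8. If 2.5 is also taken as rounded (2.45 to 2.55), the product is 0.75 × 2.45 = 1.84 to 0.85 × 2.55 = 2.17. This prints as 1.8 only near its low corner, and 2.5 reads as a chosen multiplier, not a rounded estimate.

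**3. Other ways of combining the factors at the maximum.**

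| Combination | Result |
|---|---|
| 0.8 + 2.5 | 3.3 |
| 0.8 + (2.5 − 1) | 2.3 |
| 1 + 0.8 × (2.5 − 1) | 2.2 |
| √(0.8 × 2.5) | 1.41 |
| 2.0 × (1 − 0.25), covariates explaining 25% | 1.5 |
| 2.0 × (1 − 0.50), covariates explaining 50% | 1.0 |

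None gives 1.8. The sum 0.3 + (2.5 − 1) does equal 1.8, but it takes the lower end of the wedge range and adds, so it is neither multiplicative nor a maximum.

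**4. Size, if both stated factors are right.**

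- Variance ratio: 2.0/1.8 = 1.11. Put the other way, 1.8 is 10% below 2.0.
- Standard error ratio: √1.11 = 1.054.
- Power at 2.0 for a comparison with power 1 − β at 1.8: Φ[(1.960 + z) × √(1.8/2.0) − 1.960], where z is the normal quantile for 1 − β.
  - 80%: Φ(2.802 × 0.949 − 1.960) = Φ(0.698) = 75.7%
  - 90%: Φ(3.242 × 0.949 − 1.960) = Φ(1.115) = 86.8%
- Illustration only, because the article does not itself apply the design effect to the deliveries: 12,000/1.8 = 6,667 effective births against 12,000/2.0 = 6,000.

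**5. Does it matter for the primary outcome?** The article gives no study baseline and does not say whether the hypothesised 15% increase is absolute or relative. I assumed a simple comparison of two equal halves of 12,000 deliveries and baselines from 30% to 77%, the range in the survey cited under Evidence for the integrated intervention. A 15-point absolute rise has power of about 100% at either design effect. The weakest case is a 15% relative rise from 30%, that is 30% to 34.5%:

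- At 1.8, n = 6,667/2 = 3,333 per half: power 97.6%
- At 2.0, n = 6,000/2 = 3,000 per half: power 96.2%

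**The case against.** The strongest reply is that nothing in the study depends on this number. The sample is a census of the catchment population, so no recruitment target changes. The article reports no power or detectable difference, so no printed result is falsified. The precision actually obtained will come from generalized estimating equations that allow for correlation within village clusters, with dispersion checked (Analysis for specific Aim 1). The planning design effect does not enter that model. All of this stands, and it limits the point to a planning figure.

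A reader might infer that the study's precision is overstated and that 2.0 is the true worst case. The documents do not support that. They show that three figures disagree, not which one is wrong. If the wedge maximum was calculated as 0.72, or the clustering factor as 2.25, then 1.8 is right and nothing is understated. A fuller document that is not shown may also have used a different value.

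A reader might also infer from "we further included a multiplicative design effect of 2.5 to account for cluster randomization" that the article claims a randomized design. It does not, because the Study design section says plainly that timing cannot be randomized. The phrase is a loose label for a clustering inflation and alters no number.

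The reply does not remove the mismatch itself. The factors, the rule for combining them and the result stand in consecutive sentences of intact prose, and they do not agree.

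**Conclusion.** The internal inconsistency is certain: the stated factors give 0.75 to 2.0, not a maximum of 1.8. Its direction is conditional. If 0.8 and 2.5 are both correct, the worst-case planning variance is 1.11 times that implied by 1.8, the standard error is about 5% larger, and a comparison at exactly 80% or 90% power loses about 4 or 3 percentage points. If one factor is misprinted, 1.8 may be correct.

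A reader might go further and conclude that the study is underpowered for institutional birth. Nothing here supports that. Under the assumed baselines and the simple two-group comparison, power for the primary outcome is at least 96% at either value. That illustration takes the article's design effect as given and does not test whether 2.5 or the wedge range is adequate. This is a minor correction.

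**What to change.** Reconcile the three figures in the Sample size section. If 0.8 and 2.5 are right, restate the overall design effect as 0.75 to 2.0. If 1.8 is right, correct the factor that was misprinted. Update any underlying power calculation that used 1.8, should it prove wrong. In the same sentence, describe the 2.5 as allowing for clustering of outcomes within village clusters, in line with the Study design section.

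The cost is one number and one phrase, plus a rerun of any unpublished power calculation. The sample size, the conduct of the study and the planned analysis stay as they are. If 2.0 is the right figure, the planning case becomes slightly less favourable.

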### Data collection

#### Quantitative data

All data for evaluating effectiveness outcomes (Aim One) and implementation outcomes (Aim Two) will originate from *Possible’s* CommCare system. At the community level, data are entered via the CommCare mobile application. The CommCare system automatically syncs data in near-real time on secure cloud servers. In addition, CommCare allows *Possible* to audit and track changes made in any record.

All quantitative data will be collected during program implementation, and baseline/endline measurements will signify the start/endpoints of the intervention in a particular village cluster as determined by stepped-wise implementation. All data for evaluating implementation measures related to content protocol fidelity, participation, and coverage will originate either from the CHW CommCare application or from CHN observer checklists that are filled out by a supervising CHN.

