Recognizing that women were being missed and identified late in their pregnancies, *Possible* started pregnancy surveillance for all reproductive age women. Every 3 months, women are asked about their last menstrual period and offered a pregnancy test if pregnancy is suspected. Early pregnancy detection is linked to better birth outcomes, likely due to early initiation of ANC and reduction of high risk behaviors [31]. Additionally, early pregnancy awareness is important to help women with undesired pregnancies access safe and legal abortion care.

In an effort to build social support and women’s empowerment, *Possible* began group care, based upon Centering Pregnancy [32, 33], to complement home visits. This is a model of facilitated groups throughout pregnancy that include health assessments and self-care activities; education, support, and socialization; and ongoing outcome evaluation. By bringing together pregnant women of similar gestational ages, the program makes efficient use of time for antenatal counseling and testing, while allowing facilitators to focus on women’s experiences and concerns. Women also develop a network of peer support during what can be a challenging time. In the rural Nepal context, these groups became an important modality for strengthening care and increasing trust in local village clinics and decentralizing ultrasound and prenatal lab services (Bangura A et al: Measuring fidelity, feasibility, costs: an implementation evaluation of a cluster-controlled trial of group antenatal care in rural Nepal, in preparation; Thapa P et al: Group compared to individual antenatal care: a cluster-controlled trial in rural Nepal, in preparation). These life-saving diagnostic services are not generally available at government clinics and enable CHWs to identify high-risk patients who may require referral to a higher level facility for further care and delivery.

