### Study population

The study population will include women of reproductive age (between ages 15–49) and children from 0 to 24 months of age enrolled in continuous surveillance, home-based care, and/or monthly group ANC led by *Possible’s* team in Achham and Dolakha. Specifically, this will include patients receiving health care services at Bayalpata Hospital in Achham and Charikot Hospital in Dolakha or household-level care through networks of CHWs across both districts.

Staff members involved in the program will be approached for key informant interviews (KIIs) and focus group discussions (FGDs). For all qualitative methods, we will use purposive sampling aiming to maximize heterogeneity across sex, socioeconomic position, health care issues, geographic location, age, caste-class, and other attributes. KIIs will be conducted with participants of the group ANC groups, recently delivered women, women receiving antepartum and postnatal home-based care, and reproductive age women receiving pregnancy screening. KIIs will also be conducted with team members who implemented the interventions, community leaders, and government leaders.

Participants eligible for inclusion in the study include the following: (1) married, reproductive-aged women 15–49; (2) reproductive-aged women 15–49; recently delivered in past 2 years; (3) reproductive-aged women 15–49 with active pregnancy during study period and identified by a CHW serving their village; (4) children aged 0–2 of recently delivered mothers (population 2 or 3 above); and (5) health care staff members including CHWs serving village clusters, research performance site employees involved in study design, program implementation, data collection, or data analysis processes. Study populations 1–4 must reside in either Achham or Dolakha.

Individuals meeting inclusion criteria, as stated above, will be included in the study without exclusion unless (1) individuals migrate from the study before completion of any of the integrated interventions or (2) individuals explicitly request exclusion from the study and decline to consent to the study.

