## Discussion

At the conclusion of this three-year study, we hope to assess the effectiveness and implementation of a complex and integrated RMNCH intervention delivered by CHWs in two rural districts of rural Nepal, covering a population of 300,000. As Nepal takes steps towards achieving the Sustainable Development Goals, these data will be useful in the detailed planning of a professionalized CHW cadre reaching the country’s rural population. Designed as a national pilot, the policy potential of this study is clear. However, there is likely international utility as well, given Nepal’s challenges are not unique. As a systematic review of CHW programs globally concluded, there is a need among policy makers in low- and middle-income countries for detailed implementation data, as well as data from programs brought to scale [15].

In addition to the content of the evaluation, the methodology used to conduct the evaluation will be an important contribution to the literature of implementation science. We have chosen to combine two important approaches, the type 2 hybrid effectiveness-implementation approach and the RE-AIM framework. The RE-AIM framework serves to break the implementation evaluation into five separate components, providing focus on the most important aspects of implementation for sustainable adoption of evidenced-based interventions.

The effectiveness evaluation is pragmatic and avoids the ethical challenges with having a control group when testing evidenced-based interventions. Additionally, evaluating “stepped” implementation over a three-year period allows the data to incorporate and account for some temporal trends. Each step is measured immediately prior to implementation, which is likely a stronger approach than historical controls. Perhaps the most important aspect of the chosen evaluation is that it is built within a developing health care system, and conducting research within this system strengthens data systems and quality for non-research purposes.

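### Effectiveness outcomes come only from the intervention's own care application, and the plan does not show that the period before a cluster's start is ascertained like the period after it

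*Protocol article*

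**What the plan says.** All references are to the protocol article.

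- **Source.** Quantitative data: "All data for evaluating effectiveness outcomes (Aim One) and implementation outcomes (Aim Two) will originate from" the implementer's CommCare system, and "At the community level, data are entered via the CommCare mobile application". The section Evidence for the integrated intervention describes CommCare as the CHWs' tool for surveillance, care coordination, decision support and counselling, and as the main data source for the quantitative evaluation.
- **Surveillance is part of the treatment.** Study aims lists continuous surveillance by mobile application as the second of five components. Description of the standard of care says that the government volunteers (FCHVs), who are the control condition, do not widely use mobile tools.
- **Comparison.** Analysis for specific Aim 1 measures the intervention effect in 3-month intervals against FCHV care at baseline, with calendar month as a covariate for secular trend.
- **Timing of baseline.** Quantitative data: "All quantitative data will be collected during program implementation", with baseline and endline marking where the intervention begins and ends in a given cluster. Study design: "baseline data occurs at the beginning of each step rather than at study start". Discussion: "Each step is measured immediately prior to implementation", which is given as a reason to prefer this design to historical controls.
- **Limitations.** The Discussion names the lack of a concurrent control and of randomization, geographic variation, other programmes, and variation in FCHV care. It expects the baselines to absorb the last of these. It does not mention a difference in how outcomes are found or recorded.

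**The concern.** The intervention is also the measuring instrument. When a cluster starts, it gains both the treatment and a new way of detecting and recording births, deaths and contraceptive use. A before-after contrast then estimates the treatment effect plus the change in measurement.

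The staggered start does not separate the two. Calendar month adjusts for trends shared by clusters at the same date. A change in capture that occurs at each cluster's own start is aligned with the intervention variable itself. The expectation that baselines absorb local differences in FCHV care also holds only if baseline and follow-up are measured on the same scale.

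The primary outcome has a further weakness: place of birth is recorded in the tool of the workers who prepare birth plans with women. For under-two mortality the hypothesized effect is so small that slight differences in death capture matter.

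**Working it through.** The plan gives no figure for ascertainment error, so there is none to reproduce. The calculations below show how much error would matter. Error and capture rates are assumptions.

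**Inputs from the article**
- Institutional birth rates of 30% and 77%, so up to 23% of births outside a facility at the end of the earlier survey (Evidence for the integrated intervention). These illustrate a range and are not the study baseline.
- About 12,000 deliveries in the first 18 months (8000 × 1.5 = 12,000, which agrees) and a maximum design effect of 1.8 (Sample size). The stated components give 0.8 × 2.5 = 2.0, so both values are used.
- Hypothesized effects: a 15% increase in institutional birth and 2 per 1000 fewer under-two deaths (Analysis for specific Aim 1).
- Regional under-five mortality of 82 per 1000 (Study site), used as an upper value.

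**1. Misrecorded place of birth.** Suppose a share e of home births is recorded as facility births after the start but not before. With home-birth share h, the false gain is h × e.
- 0.23 × 0.05 = 0.0115, about 1.2 points.
- 0.23 × 0.20 = 0.046, or 4.6 points.

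The gain scales with h, so a larger home-birth share would give more. If the misrecording were at baseline instead, the sign would reverse.

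**2. Differential capture of births.** Let p be the true institutional birth rate, unchanged by the intervention. Let r be home-birth capture divided by facility-birth capture at baseline, with equal capture afterwards. The observed baseline is p / (p + (1 − p)r).
- p = 0.77, r = 1.1: 0.77 / (0.77 + 0.253) = 0.753, a false gain of 1.7 points.
- p = 0.50, r = 0.9: 0.50 / 0.95 = 0.526, a false loss of 2.6 points.
- p = 0.77, r = 0.8: 0.77 / 0.954 = 0.807, a false loss of 3.7 points.
- p = 0.50, r = 1.25: 0.50 / 1.125 = 0.444, a false gain of 5.6 points.

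For p from 30% to 77%, a 10% capture difference shifts the result by about 1.7 to 2.6 points, and a 20 to 25% difference by about 3.7 to 5.6 points, in either direction.

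**3. Sampling margin.** Assume 6000 births per period (half of 12,000). The margin is 1.96 × √(DE × 2p(1 − p)/n).
- p = 0.77, DE = 1.8: 1.96 × √(1.8 × 2 × 0.1771/6000) = 0.020.
- p = 0.50, DE = 2.0: 1.96 × √(2.0 × 2 × 0.25/6000) = 0.025.

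Modest ascertainment error is therefore of the same order as random error, or larger.

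**4. What it would take to mimic the whole primary effect.** Read 15% as relative (the article does not say which). The observed baseline would have to be p/1.15.
- p = 0.30: observed 0.261, r = (0.30 × 0.739)/(0.261 × 0.70) = 1.21, so facility capture is 1/1.21 = 0.82 of home capture.
- p = 0.77: observed 0.670, r = (0.77 × 0.330)/(0.670 × 0.23) = 1.65, so facility capture is 0.61 of home capture.

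That is a large difference. Bias is more likely to distort the estimate than to create all of it.

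**5. Under-two mortality.** Missing a share s of deaths in one period shifts a rate m by m × s. Setting m × s = 2 per 1000:
- m = 82: s = 2/82 = 2.4%.
- m = 40 (assumed): s = 2/40 = 5.0%.

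Deaths missed at baseline would hide a benefit. Deaths missed afterwards would create one.

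**The case against.** **A condensed article.** Baseline questions, recall window and data collectors are details an article commonly leaves to the full protocol, and the intervention is described further in additional files not shown here. This stands, and the absence of those details is not the point. What the article does fix is the data source, the comparator and the timing, and these tie measurement to the start of treatment.

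**The timing statements can be reconciled.** Collection during implementation may refer to the stepped programme as a whole, with each cluster measured as its step opens. That is a fair reading and makes this part minor. It still needs settling, because full implementation in a sub-population takes 6 months and the claimed advantage over historical controls depends on a measurement before the start.

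**Safeguards exist.** The CommCare audit trail tracks edits to a record, not whether the place of birth is true. The supervising nurses' checklists cover fidelity, participation and coverage, not outcomes.

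**Stronger readings that the document does not support.**
- A reader might infer that no CommCare data exist before a cluster starts and that baseline births and deaths can only be recalled. The article says neither. The Discussion describes a measurement before implementation, and an earlier rollout covered 33,000 people whose overlap with study clusters is not stated.
- A reader might take "Every 3 months, women are asked about their last menstrual period and offered a pregnancy test if pregnancy is suspected" as the way later births and deaths are found. It describes pregnancy screening. Table 1 reports home-visit coverage of pregnant women and under-two children monthly.
- A reader might conclude that the primary effect is inflated. The sign depends on which births are missed or misrecorded, and the article does not allow it to be determined.
- A reader might treat hospital delivery counts by cluster as an independent estimate of the primary outcome. The study population is said to include hospital patients ("this will include patients receiving health care services at Bayalpata Hospital in Achham and Charikot Hospital in Dolakha"), and the implementer manages both hospitals. But their counts supply only part of the numerator and no denominator. They miss village clinics, other primary hospitals, home births and community deaths, and they belong to the same organization.

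**Conclusion.** The concern holds in a limited form. The plan compares one baseline around each cluster's start with follow-up in 3-month intervals, all from the intervention's own application, and does not show that the two are ascertained alike. A change in capture or recording would coincide with intervention start, would survive the calendar-month adjustment, and is not among the stated limitations.

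Under assumed error rates (5 to 20% misrecording at a 23% home-birth share, or capture differing by 10 to 25%), institutional birth shifts by about 1 to 6 points, against a sampling margin of roughly 2 to 2.5 points. For under-two mortality, 2.4 to 5% of deaths missed in one period equals the hypothesized effect. These figures show sensitivity and do not estimate actual bias. They do not make the design invalid, but they justify an inexpensive check.

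**What to change.** 1. **Like-for-like contrast.** Ascertain place of birth and child deaths at baseline and endline with the same questions and the same recall window. Pre-specify that contrast as a sensitivity analysis of the surveillance-based result. Baseline and endline measurements are already planned, so the cost is a short common module and analysis time.
2. **Agreement check.** For births that CommCare records at the two managed hospitals, report agreement with the hospitals' delivery records before and after each cluster's start. Treat this as supporting evidence only. The cost is record extraction. Other facilities and home births are not covered, and it must first be confirmed that the records can be linked to village cluster. Hospital delivery counts by cluster should not be presented as an estimate of the institutional birth rate.
3. **Text.** Reconcile Study design, Quantitative data and the Discussion on whether baseline precedes implementation in a cluster, and list differential ascertainment as a limitation. This costs only editing.
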